| Primary Outcome | Total TFI score (Score of 0-250 with high score indicating worse outcome) 6 months from starting therapy |
| Secondary Outcomes | 1) Total TFI and TFI subscale scores at 1, 3 and 12 months  2) Participant health-related quality of life measured using the EuroQol EQ-5D-5L and the Health Utilities Index Mark 3 (HUI3) responses and summary scores at 3, 6 and 12 months follow-up from starting therapy  3) Adverse events from randomisation to 3 months  4) System Usability Scale scores at 3 months  5) Qualitative feedback from focus groups and semi structured interviews at 3, 6 and 12 months  6) Cost-utility analysis synthesising costs and QALYs over trial period  7) Assess intervention adherence at 3 and 6 months |
| Number of participants | 196 participants, randomised in a 1:1 ratio |
| Eligibility criteria | Inclusion Criteria   1. Aged 18 years or over 2. Experienced tinnitus symptoms for at least 3 months and self-assessed as having a significant impact on quality of life. 3. Have access to a smartphone 4. Able and willing to give consent for the study prior to participation 5. Able to speak and read English to a sufficient level.   Exclusion Criteria   1. Tinnitus with potential “red flag” symptoms i.e. unilateral or pulsatile tinnitus (assessed via a red flag checklist during the screening call) 2. Significant mental health problems e.g. history of suicidal ideation or requirement for psychiatric/psychological support beyond Primary Care level 3. Have required hospitalisation for depression or taking antipsychotic drug 4. Currently taking part in another clinical trial for hearing/tinnitus 5. Awaiting surgical intervention for hearing/tinnitus 6. Previously undergone tinnitus therapy of any type e.g. CBT or TRT 7. Pregnant and breastfeeding women   Additional Note: Patients with hearing aids are eligible to participate in the study |
| Intervention | The Oto digital programme for tinnitus. This involves direct access to a digital multi-modal therapy package incorporating CBT, physical therapy, mindfulness and relaxation therapy. |
| Comparator | Current standard of care (1-1 therapist-delivered CBT). |
| Duration of study | 18 months |
| Randomisation / Blinding | Randomised 1:1 by computer algorithm and stratified by age, sex and level of hearing loss. Unblinded. |
| Statistical analysis | Non-inferiority |
| Intervention Adherence | Number of participants in each group completing therapy programme by 3 months |

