# 11. HEALTH ECONOMIC EVALUATION

## 11.1 Health Economic Evaluation

A health economic evaluation forms an integral part of the trial and will be conducted from the perspectives of the NHS, personal and the society. The economic evaluation will take the form of a cost-utility analysis with a one-year time horizon using quality-adjusted life years (QALYs) as the main outcome measure. Although the clinical study has a non-inferiority design and our hypothesis is that QALYs will be similar between the Oto app and standard care, there is no prior hypothesis that costs will be similar between groups. Therefore, a standard economic evaluation framework will be used to synthesise differences in costs and QALYs between study arms using the incremental cost-effectiveness ratio (ICER)^8^.

We will follow all participants from baseline to 12 months and will collect information about the delivery of the intervention (app and standard care), primary and community health care, visits to accident and emergency (A&E) and prescribed medications. We will focus on the collection of resource utilisation related to tinnitus. Data will be collected using bespoke questionnaires that will be embedded into the Lindus Health EDC platform for participant completion at regular intervals during follow-up (weeks 12, 26 and 52). Unit costs from recognised national sources including the new NHS National Cost Collection, the Personal and Social Services Research Unit (PSSRU), and the NHS Electronic Drug Tariff will be used to value NHS health care resource use. To understand the burden beyond the health service, we will ask participants about any related out-of-pocket expenses (e.g. hearing aids, complementary and alternative paid treatments) and any time away from paid employment due to the condition.

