Tinnitus is known to impair aspects of daily health-related quality of life (HRQoL) and such information will be collected in the study. For the purpose of the economic evaluation, HRQoL instruments that are preference-based are required for QALY estimation. In this study we will administer the EuroQol EQ-5D-5L and the Health Utilities Index Mark 3 (HUI3)^9^. Both questionnaires are short and the EQ-5D-5L covers descriptive levels for five dimensions (mobility, self-care, usual activities, pain/discomfort, and anxiety/depression) whereas the HUI3 covers descriptive levels for eight dimensions (vision, hearing, speech, ambulation, dexterity, emotion, cognition and pain). The health state described in each measure is converted into a single value on a scale where death is anchored at 0 and perfect health at 1 using value sets. The EuroQol EQ-5D is currently the preferred preference-based instrument to measure HRQoL in adults by the National Institute for Health and Care Excellence (NICE) and we will be using the interim 5L- > 3L mapping tool to estimate utility values^10^. To calculate utility values from HUI3 responses we will use the Canadian tariff as a UK-specific value set is currently not available. The questionnaires will be administered at baseline and at all follow-up points (weeks 4, 12, 26 and 52). QALYs for each participant over the trial period will be calculated and will be derived by estimating the area under the curve of the profile generated connecting estimates of HRQoL at each time point using linear interpolation. If necessary, any baseline imbalances in HRQoL at baseline and resulting QALYs will be adjusted using regression methods. QALYs will be derived from utility values from the EQ-5D-5L and HUI3 but the former will be used in the base case analysis.

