​​To understand the burden for participants and wider society, healthcare costs will be reported separately from any out-of-pocket expenses and any societal productivity losses. When analysing continuous variables (for example costs, HRQoL scores, QALYs) means and standard deviations will be computed for each trial arm and for comparisons between trial arms, mean differences and 95% parametric confidence intervals will be used. Mean differences in costs and QALYs between study arms will be synthesised using ICERs and to facilitate interpretation, net benefit statistics will be calculated^11^. Uncertainty around net-benefits will be expressed using confidence intervals (if feasible) and cost-effectiveness acceptability curves^12^. Deterministic sensitivity analysis will be used to address uncertainty around study parameters (e.g. unit costs) not participant to sampling variation. Data completeness on resource use and HRQoL will be closely monitored on a regular basis and missing data mechanisms discussed. Multiple imputation will be implemented to handle missing data if a complete case analysis results in substantial loss of information that could bias our results^13^. All analyses will be conducted and reported in accordance with existing good practice guidelines for economic evaluation^14,15^.

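### QALYs are adjusted for baseline utility only at discretion, so the base-case incremental QALY is not fixed in advance and loses precision when no adjustment is made

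*Protocol*

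**What the plan says.** Protocol section 11.1 plans a "cost-utility analysis with a one-year time horizon using quality-adjusted life years (QALYs) as the main outcome measure". Each participant's QALY is obtained by "estimating the area under the curve of the profile generated connecting estimates of HRQoL at each time point using linear interpolation", so baseline utility is the first point of the curve.

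On adjustment, the section says: "If necessary, any baseline imbalances in HRQoL at baseline and resulting QALYs will be adjusted using regression methods". It gives no threshold, model or covariate list, and does not say when the decision is taken. For costs, HRQoL scores and QALYs alike it then says that "for comparisons between trial arms, mean differences and 95% parametric confidence intervals will be used", and that "Mean differences in costs and QALYs between study arms will be synthesised using ICERs", with net benefit statistics built on the same quantities.

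The visit schedule for utilities is inconsistent. Section 11.1 places both questionnaires at baseline and weeks 4, 12, 26 and 52. The synopsis has "summary scores at 3, 6 and 12 months follow-up from starting therapy", and section 4.1, the month 1 visit in section 7.10.1 and the schedule in Appendix 2 also omit week 4.

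Randomisation is stratified by age, sex and hearing level (section 7.6), not by utility. Baseline questionnaires are completed after randomisation is confirmed and before treatment starts (section 7.7).

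**The concern.** Baseline utility is a component of the QALY and would also be expected to predict every later utility. It is therefore worth adjusting for whether or not the arms look unequal. A rule that adjusts only when someone judges it necessary has two faults.

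- **Discretion.** The base-case estimator is chosen after the baseline comparison is known. Nothing requires the choice to be made before follow-up utilities are seen, and the trial is open-label.
- **Lost information.** When the gap is judged small enough to ignore, the estimate still carries that gap, and the interval for the incremental QALY is wider than it need be.

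The incremental QALY is the denominator of the ICER and one of the two parts of net benefit. Section 11.1 expects QALYs to be similar between arms, so the quantity is likely to be small and its precision matters.

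**Working it through.** The protocol states no precision, SD or correlation for utilities, so there is no figure of its own to reproduce.

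**Inputs from the protocol.** 196 participants randomised 1:1 (98 per arm); 10% attrition (section 10.2), so 98 × 0.90 ≈ 88 per arm; a one-year area under the curve by linear interpolation; two versions of the visit schedule.

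**Assumptions.** Equal variance σ² at each visit and the same correlation r between any two visits. Where an absolute size is shown, utility SD is taken as 0.20.

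**Step 1: weights (trapezoid rule).**
- 0/3/6/12 months: (1.5, 3, 4.5, 3)/12 = 0.125, 0.25, 0.375, 0.25. The sum of squares is S = 0.281.
- 0/4/12/26/52 weeks: (2, 6, 11, 20, 13)/52 = 0.038, 0.115, 0.212, 0.385, 0.25. S = 730/2704 = 0.270.

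**Step 2: variance removed by always adjusting.** With baseline weight w0:
- Var(QALY)/σ² = S + r(1 − S)
- Cov(QALY, baseline)/σ² = w0 + r(1 − w0), which is also the regression slope
- share of variance removed = Cov² / (Var × σ²); interval width factor = √(1 − share)

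For months with r = 0.5: Var = 0.641σ², Cov = 0.5625σ², and 0.5625²/0.641 = 0.494.

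| Schedule | r | Var/σ² | Cov/σ² | Variance removed | Width factor |
|---|---|---|---|---|---|
| 0/3/6/12 months | 0.3 | 0.497 | 0.388 | 30% | 0.84 |
| 0/3/6/12 months | 0.5 | 0.641 | 0.563 | 49% | 0.71 |
| With week 4 | 0.3 | 0.489 | 0.327 | 22% | 0.88 |
| With week 4 | 0.5 | 0.635 | 0.519 | 42% | 0.76 |

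These shares do not depend on the assumed SD. Any positive r gives the same direction.

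**Step 3: size in QALYs (SD 0.20, 88 per arm, r = 0.5).** The standard error of the chance gap in baseline utility is 0.20 × √(2/88) = 0.030. A one-standard-error gap moves the unadjusted QALY difference by 0.5625 × 0.0302 = 0.017 (months), or 0.519 × 0.0302 = 0.016 (with week 4). The unadjusted 95% half-width on the monthly schedule is 1.96 × 0.20 × √(0.641 × 2/88) = 0.047; adjusted, it is 0.047 × 0.711 = 0.034.

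**Step 4: one possible reading of the discretionary rule.** Suppose adjustment is made only when the baseline difference is significant at 5%. In 20,000 simulated trials (0/12/26/52 weeks, r = 0.5, SD 0.20, 88 per arm, no true difference) the standard error of the incremental QALY was 0.0242 never adjusting, 0.0225 under the rule and 0.0173 always adjusting. The rule was triggered in 5% of trials. It recovered about a quarter of the available gain: (0.0242 − 0.0225)/(0.0242 − 0.0173) ≈ 0.25. When the gap lay between 1 and 1.96 standard errors in one direction, the unadjusted estimate was off by 0.023 QALY on average, and the adjusted one by about 0.

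**Step 5: net benefit.** For willingness to pay λ, Var(net benefit) = λ²Var(ΔQALY) + Var(ΔCost) − 2λCov(ΔQALY, ΔCost). Adjusting for baseline utility acts mainly on the first term and may barely reduce the cost variance, so the percentages in Step 2 do not carry over to net benefit.

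**The case against.** **The default is inferred.** The protocol never describes the comparison as unadjusted, and an arm coefficient from a regression is also a mean difference with a parametric interval. Section 10 defers detail to a separate SAP. This stands as far as it goes. However, section 11.1 states a conditional rule for this specific estimator. That differs from leaving the model unspecified, and no other section overrides it. The covariate rule in section 10.1 concerns repeated-measures models for secondary outcomes and does not name baseline utility.

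**Stronger readings.** A reader might infer three things that the documents do not support.
- *That the unadjusted result is biased.* Under 1:1 randomisation it is not biased on average, and its ordinary interval already allows for chance imbalance. In Step 3 the shift of 0.017 sits inside a half-width of 0.047. If true QALYs are equal, the sign of the difference is a matter of chance with either estimator.
- *That a QALY test gains power.* Section 11.1 plans ICERs, net benefit and acceptability curves. It plans no QALY hypothesis test and states no power for one.
- *That the whole cost-utility result narrows by the same percentage.* The narrowing applies to the incremental QALY (Step 5).

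**Adjustment has a risk here.** Participants are told their allocation (section 7.6) and baseline utility is reported after randomisation (section 7.7), so it could respond to that knowledge. Suppose it shifts reported baseline by d and leaves later utilities unchanged. With monthly weights and r = 0.5, the unadjusted difference is off by 0.125d and the adjusted one by 0.125d − 0.5625d = −0.4375d. This is a scenario, not a demonstrated effect, but it is a real caveat on the fix. Discretion does not solve it either.

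**Conclusion.** The point holds for the incremental QALY. Section 11.1 fixes a data-dependent rule where a pre-specified one is available from data already collected. The cost is analyst discretion, error conditional on the realised baseline gap, and lost precision when no adjustment is made. Always adjusting would remove about 30% to 49% of the variance of the incremental QALY on the 0/3/6/12-month schedule, or 22% to 42% if week 4 is collected. Both ranges are for r from 0.3 to 0.5 under equal variances and equal correlations, which are assumptions. The absolute QALY figures also rest on an assumed SD of 0.20. The gain in net benefit is smaller and cannot be quantified from the protocol. The matter concerns a secondary outcome and leaves the primary non-inferiority comparison untouched.

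**What to change.** In section 11.1, remove the opening condition from the adjustment sentence. State that the base-case incremental QALY, and the net benefit built from it, come from a regression of QALY on arm, the participant's baseline utility from the same instrument, and the stratification factors, whatever imbalance is observed. Set the factor coding in advance: hearing has seven categories in section 7.6 and sparse ones should be collapsed, and the age bands as written leave 40 and 61 unassigned. Report the unadjusted difference as a sensitivity analysis.

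Reconcile the week 4 utility collection between section 11.1 and the synopsis, section 4.1, section 7.10.1 and Appendix 2, since it changes the QALY weights.

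Preferably have the baseline EQ-5D-5L and HUI3 completed before allocation is disclosed, which removes the risk that reported baseline responds to allocation. If that is not possible, name the risk and show the unadjusted result alongside the base case.

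The cost is a few sentences in the protocol and the analysis plan. No new data are needed. Moving the baseline forms earlier is a change of order in the enrolment process. Participants without a baseline form would need the multiple imputation that section 11.1 already provides for conditionally.

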## 10.1 Description of Statistical Methods

The primary analysis will be conducted on the intention-to-treat (ITT) population. In addition to this, a per-protocol analysis will also be planned as a sensitivity analysis. Compliance will be defined as a minimum of 60 minutes of total use for the intervention group, and one or more sessions for the CBT group. Participants reporting poor compliance will be recorded and these participants will be included in the ITT analysis. Adherence to the smartphone app delivered programme will be monitored through the app with results analysed by intention-to-treat (ITT).

The primary outcome will be reduction in total TFI score at the 6 month point in the ITT population. Non-inferiority will be assessed by constructing a 95% confidence interval around the mean difference in TFI reduction between the groups, and comparing the -upper bound of the confidence interval to the pre-specified non-inferiority margin.

A secondary analysis of the primary outcome will examine significant differences between the control and intervention group’s TFI score at 6 months using a general linear model or a comparable suitable method, using the stratification variables and other potential confounding variables as covariates.

As a sensitivity analysis, the primary outcome will be analysed using the Per-Protocol (PP) population, which consists of participants complying with the treatment regimen. Compliance will be defined as a minimum of 60 minutes of total use for the intervention group, and one or more sessions of CBT for the control group.

Secondary outcomes will be compared between groups and over time with mixed-effects regression models for repeated measures, using the stratification variables and other potential confounding variables as covariates. Logistic models will be used for binary outcomes, and Gaussian models for continuous outcomes. An interim analysis may be conducted once a sufficient number of participants have completed the 6 month milestone. The results of the interim analysis do not influence the continuation of the trial.

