## 10.4 Handling of Missing and Incomplete Data

The Citrus EDC provides real-time notifications to the trial team to inform them of any missing data to minimise the risk of missing data. For patient reported outcomes, the EDC will notify the study team if assessments are overdue so the study team can follow up and collect these outcomes (the trial team will contact the patient up to 3 times). If a patient reported outcome is not completed within the scheduled window, the data will be considered missing with reasons provided. For clinician reported outcomes the EDC system will flag if an outcome is missing. Missing data will be managed according to Lindus Health SOPs. Missing data will be reported with reasons given where available and imputed using multiple imputation for the ITT population. Depending on the extent of missing values, further investigation may be made into the sensitivity of the analysis results to the method(s) specified.

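### EQ-5D-5L and HUI3 scores fall under two missing-data rules, and the cost-utility base case may be a complete-case analysis chosen after the data are seen

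*Protocol*

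**What the plan says.** Protocol section 10.4 first defines when a questionnaire counts as missing: "If a patient reported outcome is not completed within the scheduled window, the data will be considered missing with reasons provided". It then gives the remedy: "Missing data will be reported with reasons given where available and imputed using multiple imputation for the ITT population". No outcome is exempted and no trigger is set. What depends on the amount of missing data is only the extra sensitivity work: "Depending on the extent of missing values, further investigation may be made into the sensitivity of the analysis results".

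Section 11.1 sets its own scope: "When analysing continuous variables (for example costs, HRQoL scores, QALYs) means and standard deviations will be computed for each trial arm". Its missing-data rule is conditional: "Multiple imputation will be implemented to handle missing data if a complete case analysis results in substantial loss of information". The clause goes on to require that this loss be one that could bias the results. The section also promises to monitor completeness and to discuss missing-data mechanisms. QALYs are to be "derived by estimating the area under the curve of the profile generated connecting estimates of HRQoL at each time point", with linear interpolation. No analysis population is named for the economic evaluation.

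The synopsis has, as the second of its secondary outcomes and with follow-up visits in months 3, 6 and 12, this entry: "Participant health-related quality of life measured using the EuroQol EQ-5D-5L and the Health Utilities Index Mark 3 (HUI3) responses and summary scores". The cost-utility analysis is a separate entry, outcome 6. For secondary outcomes generally, section 10.1 says: "Secondary outcomes will be compared between groups and over time with mixed-effects regression models for repeated measures". Section 7.11 ends assessments at withdrawal but keeps whatever was recorded up to then in the intention-to-treat analysis.

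**The concern.** An analyst handling the EQ-5D-5L and HUI3 scores cannot tell which rule applies. Section 10.4 says impute. Section 11.1 says impute only if a complete-case analysis turns out to lose too much.

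For costs and QALYs, the conditional wording makes complete case the working default, and the decision to leave it can be taken only after the data have been examined. In an open-label trial, a comparison restricted to people who returned their forms is no longer clearly a comparison of the randomised groups. It also discards information already collected: someone who withdraws after month 6 has supplied utilities at baseline, 3 and 6 months, and a complete-case QALY uses none of them.

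At stake is the economic result that section 3.2 offers as evidence of value for money to the NHS and society. Section 11.1 says there is no prior expectation that costs will be similar between the arms.

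**Working it through.** The point rests mainly on comparing the text; the protocol gives no figure for complete economic data that could be reproduced.

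**Step 1: the two rules side by side**

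| | Section 10.4 | Section 11.1 |
| --- | --- | --- |
| Data covered | Patient-reported outcomes, no exemption | Costs, HRQoL scores, QALYs |
| Is imputation conditional? | No | Yes, on a substantial and potentially biasing loss under complete case |
| Role of the extent of missingness | Decides on extra sensitivity work only | Decides whether to impute at all |
| Population | ITT | Not stated |

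The overlap is the EQ-5D-5L and HUI3 scores. They are patient-reported secondary outcomes under section 10 and are named again, as HRQoL scores, in section 11.1.

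**Step 2: who is left out of a complete-case QALY**

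The QALY is an area under the utility profile to 12 months. A participant who withdraws before month 12 has no closing point, so a complete-case analysis omits that person. Section 7.11 nevertheless commits the earlier data to the ITT analysis. Resource-use forms work the same way: a 12-month cost has a gap if a later form is absent.

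**Step 3: size from the documented figure**

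Inputs: 196 randomised and 10% attrition, both from section 10.2. Assumption: all of that attrition, and no more, has happened by month 12.

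- Complete cases: 196 × (1 − 0.10) = 176.4, about 176.
- Left out: 196 − 176 = 20 participants.
- Standard error relative to full data: 1/√0.9 = 1.054, about 5% larger.

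**Step 4: intermittent missingness, illustration only**

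Assumptions: the 10% attrition above, plus a proportion m of forms missing independently at each of four utility visits (baseline, 3, 6 and 12 months), with any missed form making the QALY incomplete. The protocol documents none of these values of m.

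Complete cases = 196 × 0.9 × (1 − m)⁴

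- m = 3%: about 156
- m = 5%: about 144
- m = 10%: about 116

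These counts overstate the loss if a single missed middle visit is bridged by interpolation. Even the set of visits is unsettled: section 11.1 adds a week 4 utility questionnaire that section 4, section 7.10.1 and the schedule in Appendix 2 do not contain.

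**The case against.** The best reply is that sections 10 and 11 specify different analyses. The synopsis lists HRQoL scores and the cost-utility analysis as separate outcomes, and an economic evaluation may have its own missing-data rule. If 11.1 governs only costs and QALYs, most of the conflict goes. That is fair, but the protocol does not draw the line: 10.4 exempts nothing, and 11.1 names HRQoL scores in its own scope. Drawing the line would also leave the conditional complete-case default in place for the cost-utility analysis.

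A second reply is that the trigger in 11.1 includes potential bias, so imputation is called for in the very situation that is feared. This stands in part. The authors recognise the problem, but the judgement is still made after the data are seen. That the protocol puts no number on the trigger is not the complaint, since such detail can be left to the SAP.

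Some stronger readings are tempting and should not be adopted:

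- **That the QALY analysis breaks ITT.** Section 11.1 names no population, and complete case as the default is implied by its conditional wording rather than stated. The documents support only that the analysis may leave out participants whose data section 7.11 says will be kept.
- **That an imputed HRQoL result will disagree with a complete-case QALY result.** Section 10.1 uses mixed models, which can use every observed visit, so such a discrepancy is not established.
- **That any missed form voids a QALY.** Section 11.1 interpolates linearly and does not say this. Withdrawal before month 12 is the clear case.
- **That precision falls by a known larger amount.** Taking 10% of forms as missing independently at each of three follow-ups gives 0.9³ = 0.729, or 143 of 196, and a standard error 17% larger. The protocol's 10% is an overall attrition allowance, not a per-visit rate, so it does not support that figure.

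**Conclusion.** The point holds as a matter of consistency and of analysis choice. The EQ-5D-5L and HUI3 scores are under two rules. The cost-utility base case may be a complete-case analysis, decided on after the data are seen, that drops partial utility and cost data.

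The only size the documents support is about 176 of 196 with complete data, resting on the assumption that the planned 10% attrition all occurs by month 12 and nothing else is missing. Further intermittent missingness would reduce the number, by an undocumented amount. The 5% larger standard error compares complete case with full data. It does not measure what imputation would gain, because imputation cannot recover all of the lost information. No bias can be quantified from the protocol.

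The matter is of moderate weight: it affects a secondary outcome and the economic evaluation, and leaves the primary TFI non-inferiority test untouched.

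**What to change.** In section 11.1, replace the conditional sentence with a prespecified rule along these lines: *missing utilities and costs will be multiply imputed for all randomised participants (ITT), using baseline and all observed visits, and this will be the base case; a complete-case analysis will be reported as a sensitivity analysis.*

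Imputing separately by arm is advisable, but it would be an addition, since section 10.4 does not specify it.

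Add one sentence stating that section 10 governs the comparison of EQ-5D-5L and HUI3 scores as secondary outcomes, and section 11 governs costs and QALYs. Settle at the same time whether utilities are collected at week 4, so that the visits entering the imputation and the QALY are fixed.

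A scope sentence alone would remove the contradiction, but the economic base case would still depend on a choice made after seeing the data. The full change costs a few lines of text and slightly more analysis work. It needs no new data and no change to the primary analysis.
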